### Inclusion and exclusion criteria

This study will include children in fifth grade of primary school between 9 and 11 years old. Table 1 contains the criteria for including data from children in the controlled trial.

**Table 1 tbl0001:** Inclusion and exclusion criteria.

Inclusion criteria	Exclusion criteria
1. Children of both sexes.	1. Children with uncorrected sensory impairment.
2. Children who at the time of the beginning the study are between 9 and 11 years old.	2. Children with a psychiatric diagnosis.
3. Children enrolled in fifth grade of primary school in an educational institution of Ibagué, Colombia.	3. Children who exceed the age range at the beginning of the pre-test.
4. Children with typical cognitive development.	4. Children with previous experience in computational thinking, coding or programming training.
5. Children who have participated in 70% of the intervention.	5. Children who have joined the educational institution after the application of the pretest.

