### Recruitment

We evaluated the possible causes of loss from the sample: (1) subjects who did not meet the inclusion factors for the sample, especially the age of the children; (2) dropout rate for this school grade, which is usually around 15%; consequently, for the recruitment we decided to include 4 fifth grade school groups from the same public educational institution in the city of Ibagué, Colombia. Among the four courses, it is expected to convene approximately 100 children, so that the final sample for the analysis has the minimum projected size.

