### Bias control

We used the Cochrane organization's control for bias tool for controlled trials [70] which covers six bias domains. Table 3 shows the actions established to control the appearance of the most common types of bias in non-clinical studies: selection, detection, performance, performance, desertion and reporting [71].

**Table 3 tbl0003:** Cochrane risk of bias check tool.

Bias		Description
Selection bias	Sequence generation	An investigator from outside the study will randomize the school groups to the interventions.
	Allocation concealment	A qualified evaluator outside the research group will be in charge of the evaluation. This evaluator will be blind to the group assignment and the nature of the intervention.
Performance bias	Blinding of participants and staff	The evaluator will be blind to the intervention. Since the control group will be treated as usual, blinding among the participating subjects will not be possible
Detection bias	Blinding of assessors to outcome.	The evaluators will be blind to the type of intervention applied. The investigator in charge of the intervention will be blinded to the results of the evaluation.
Attrition bias	Incomplete outcome data.	Data from participants who complete less than 70% of the training will be excluded from the study. We will perform data imputation; for this, we will evaluate the difference of the results with the data of the excluded subjects and without them.
Reporting bias	Selective reporting of results	We will present the results in accordance with the objectives set out in the trial registration.

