### Statistical analysis plan

A hypothesis test will be conducted through Mixed Repeated Measures Analysis of Variance (ANOVA MR) with Bonferroni corrections to look at the differences between groups, in which the pre-test, post-test, and follow-up measures will be the factor of repeated measures. (Within-subject) and the difference between the experimental and control groups as the subject factor. The effect size will be measured with partial eta squared. The assumptions of this type of analysis assume a continuous metric-dependent variable with approximately normal distribution and with homoscedasticity in each of the groups.

A multivariate linear regression analysis will also be performed to assess the correlations between cognitive measures and computational thinking. And logistic regressions to analyze binary variables to evaluate the association between the covariates and the results.

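### The attrition row calls a with/without comparison of low attenders imputation; it fills in no unmeasured score and is paired with a three-measure ANOVA that normally needs complete cases

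*Protocol article*

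**What the plan says.** Three parts of the protocol article bear on missing scores.

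- **Bias control, Table 3, attrition row.** "Data from participants who complete less than 70% of the training will be excluded from the study". The next sentence reads: "We will perform data imputation; for this, we will evaluate the difference of the results with the data of the excluded subjects and without them". Table 1 also lists the 70% threshold as an inclusion criterion: "Children who have participated in 70% of the intervention".
- **Recruitment.** The article cites a "dropout rate for this school grade, which is usually around 15" per cent, and responds by recruiting four classes: "it is expected to convene approximately 100 children, so that the final sample for the analysis has the minimum projected size".
- **Statistical analysis plan.** "A hypothesis test will be conducted through Mixed Repeated Measures Analysis of Variance (ANOVA MR) with Bonferroni corrections", and "the pre-test, post-test, and follow-up measures will be the factor of repeated measures". The section does not mention incomplete cases or imputation.

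The Protocol design section says that the three-month measure (T3) is applied to the experimental group. The abstract, the opening of that same section and the statistical analysis plan describe three measures without that restriction.

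**The concern.** Imputation replaces scores that were not measured. What Table 3 describes after announcing imputation is running the analysis with and without a set of children defined by attendance. That is a reasonable sensitivity analysis, but it answers a different question: whether low attenders change the result. A reader of the attrition row would believe that missing scores are dealt with, when the step described does not do that.

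The choice of primary analysis makes this matter. A conventional repeated-measures ANOVA with three levels needs all three scores per child. A child absent only at T3 would then normally drop out of the T1 to T2 comparison too, although both scores exist. If the children lost differ from those kept, and do so more in one arm, the between-arm comparison of change is biased. Recruiting more children protects the sample size but not against that bias.

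**Working it through.** **1. Which children the Table 3 step reaches**

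- Below 70% attendance, still at the school: can be tested at T2, so nothing needs imputing. The with/without comparison can use the observed scores.
- Below 70%, left the school: among the excluded children, but T2 and T3 do not exist. Including them in the comparison would require filled-in values, and the row describes no way of obtaining them.
- At least 70%, then missed T2 or T3: not an excluded child, so the row does not apply. The article does not say how many to expect.

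**2. The stated sample size, and whether loss threatens it**

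Inputs from Table 2: effect size 0.25 (lower end of the range, taken as Cohen's f because the metric is not named), two groups, three measures, alpha 0.05, power 0.95. Assumed: correlation 0.5 between measures and sphericity. For the group-by-time interaction:

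- noncentrality = f² × N × m / (1 − ρ) = 0.0625 × 44 × 3 / 0.5 = 16.5
- degrees of freedom = (2 − 1)(3 − 1) = 2 and (44 − 2)(3 − 1) = 84
- power = 0.956, so the stated 44 reproduces.

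With about 100 children and 15% loss, 100 × 0.85 = 85 remain. Enrolment needed for 44 after 15% loss is 44 / 0.85 = 51.8, so 52, well below 100. Loss would have to reach 56% before 100 fell to 44. Only if enrolment were itself 44 would power suffer: 44 × 0.85 = 37.4, and power at 37 to 38 children is 0.91 to 0.92.

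**3. Size of the possible bias**

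Assumptions, none of them given in the article: 15% are lost between T1 and the later measures; in one arm they average d SD below the pre-test mean; in the other arm loss is unrelated to score; the pre/post correlation is 0.6 with equal variances.

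- Shift in the retained pre-test mean = 0.15 × d / 0.85. For d = 1 this is 0.176 SD.
- Slope of change on pre-test = −(1 − 0.6) = −0.4.
- Bias in change, absolute size, d = 1: 0.4 × 0.176 = 0.07 SD.
- d = 0.5: 0.4 × 0.088 = 0.035 SD.
- d = 1.5: 0.4 × 0.265 = 0.106 SD.

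The sign is negative for the arm that loses low scorers, because the children kept start higher and regress.

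A simulation on different assumptions agrees in order of size (50 per arm, correlation 0.5, 15% of 50 rounded down to 7 lost per arm, no true effect, 400 runs). When one arm lost mainly low pre-test scorers, the difference in change among retained children was −0.10 SD. When loss was random in both arms it was 0.01 SD, about one simulation standard error: √(2/43) / √400 = 0.011.

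**4. T3 in the controls**

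If T3 is measured only in the experimental group, every control child lacks the third level of the within-subject factor. A complete-case three-measure comparison would then contain no controls.

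**The case against.** The strongest reply is that the article never says children with a missing score are deleted, nor that leavers' scores go unimputed. It does announce imputation; the method, variables and time points normally belong in the full plan, which is not shown. The sentence can also be read as imputing the excluded children's missing scores and then comparing results with and without them. Children who leave before 70% of the sessions fall in that group.

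Much of this stands. A reader might infer that leavers are certainly never imputed and are removed entirely; the documents do not support that. Listwise deletion is the usual behaviour of the method, not a stated rule. A reader might also see a contradiction in needing post-test scores from excluded children. That is not established either: the rule can be an exclusion from analysis, and nothing says low attenders go untested.

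The size is open to challenge too. The figure of 100 is the number expected to be convened, before eligibility losses. The 15% has no stated time window, so it is not shown that 15 tested children would be lost. Both arms come from one grade of one school, and nothing in the article indicates that leaving depends on arm. How the 70% rule applies to controls is unclear, so unequal exclusion cannot be ruled out.

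What the reply does not remove is that the procedure actually described is not imputation, does not cover a child with adequate attendance who misses T2 or T3, and sits beside an analysis that normally requires all three scores.

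**Conclusion.** The point holds as a mislabelled procedure combined with an ill-suited analysis, not as proof that children will be deleted. This is more than missing detail, because a stated safeguard does not do what its name says. The bias in change is about 0.035 to 0.11 SD under the one-arm selective loss set out above, and near zero if loss is alike in both arms. The stated 44 is safe at the expected recruitment, so the issue is bias and discarded scores rather than power. The conflict over who has T3 is the more basic obstacle: read literally, it leaves the three-measure comparison without complete control cases whatever the dropout. The change is worth making before the data are analysed.

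**What to change.** 1. Replace the Table 3 sentence with a rule that every child still at the school is tested at the scheduled T2 whatever the attendance, and is included in the main analysis. Bring the 70% criterion in Table 1, which is known only after randomisation, into line with this.
2. Replace the repeated-measures ANOVA with a likelihood-based mixed model that uses all available scores, names the between-arm contrast at T2, and accounts for class. Correctly specified, it removes bias when loss depends on the observed pre-test; it does not cure loss that depends on unmeasured scores. How far four classes allow class to be modelled is a separate matter.
3. Keep the run without low attenders, call it a sensitivity analysis, and report losses by arm with pre-test means.
4. Reconcile the Protocol design section with the statistical analysis plan on who has T3. If controls are not measured at T3, do not impute it for them: with no observed control value, imputation within arm has nothing to work from.

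The cost is revised wording, a different model command and a little more analysis work. No extra children and no test beyond the scheduled T2 are needed.

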### Outcome measures

#### Primary outcome measures

To measure the executive functions of children we have selected neuropsychological tests with recognition and reliability studied. Table 4 contains the selected instruments and the rating parameters.

**Table 4 tbl0004:** Description of primary measures.

Variable	Test	Rating Parameters	Authors
Sequential planning	London Tower	Time since start Execution time Number of moves Number of rule violations	Shallice [72]
Visuospatial planning	Porteus maze, BANFE-2 version.	Number of times it traverses. Number of dead ends Execution time	Flores-Lázaro et al. [73]
Auditory-verbal working memory	WISC-V Digit Scale	Number of right answers in direct order, reverse order and increasing order Digit span in forward order Digit span reverse order Digit span increasing order	Wechsler [74]
Visual spatial working memory	Corsi cubes, version WMS-III	Maximum number of elements Number of correct trials	Corsi [75] Wechsler [76]
Visual working memory	WISC-V Span of drawings Scale	Span of drawings Span of stimuli	Wechsler [74]
Cognitive flexibility	M-WCST Wisconsin cards abridged version	Number of right answers Number of maintenance errors Number of perseverations Number of deferred perseverations Execution time Completed Categories	Arango-Lasprilla et al. [77] Schretlen [78]
Inhibitory control	Classic stroop test	Number of stimuli words, letters and words/letters	Golden [79]

#### Secondary outcome measures

The study will also include secondary variables such as level of satisfaction with training, computational thinking, metacognition, and attention. Table 5 presents the instruments selected to measure these variables.

**Table 5 tbl0005:** Description of secondary measures.

Variable	Test	Rating Parameters	Authors
Computational thinking	CTt scale	Number of right answers	Román-González et al. [[46], [80], [81]]
Metacognition	Metacognition test	Items on a Likert scale. The test is divided into six factors: Knowledge, control and supervision, planning, experiences, evaluation and strategies	Jaramillo-Mora & Osses-Bustingorry [82]
Metamemory	Metamemory scale BANFE-2 version	Number of total errors Number of negative errors Number of positive errors Perseverations Intrusions	Flores-Lazaro et al. [73]
Attention	Trail Making Test TMT D2 Test	Execution time number of errors Number of right answers Number of correct answers minus errors	Portellano y Martínez [83] Brickenkamp, et al. [84]
Satisfaction, acceptability, adherence and feasibility	Satisfaction and adherence scale	Likert scale with 4 response options	Designed by the authors based on Attkisson and Zwick [85]

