### Interventions

#### Experimental group

The experimental group will participate in a training in computational thinking called COGNI-MACHINE, designed by the first author. The intervention comprises 24 sessions; each session will be structured as a workshop and will take place in the computer room of the participating educational institution. The intervention will last 12 weeks, with two sessions per week of 60 min each.

The training workshops will be based on the principles of problem-based learning, and the activities will be designed following the principles of low floor / high ceiling. For the design of the computational thinking intervention, the following sources were taken into account: (1) The recommendations emerging from the results of the previously conducted pilot test [[30], [45]]; (2) A broad review of activities, projects, and courses available to teach computational thinking in school contexts; (3) A systematic review of background and similar studies.

To select the plugged and unplugged activities that would be part of the training, we reviewed: (1) Existing open-access training and existing repositories of unplugged activities; (2) The integrated development environments available to learn to code in blocks; 3) The educational robotics devices available in the market for Colombia. From these reviews, unplugged activities were selected from different sources such as CS Unplugged, code.org, programemos.com, and Mintic's “Coding for kids” [88]. Lessons from courses B, C, and D of the code.org integrated development platform and the Makecode integrated development platform were selected for the block programming activities. For the plugged projects, he selected the micro:bit V2 microprocessor (see Fig. 2), which is a small programmable board designed by the BBC which has several integrated sensors, Bluetooth connection, radio frequency, push buttons, and LED light outputs.

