## Discussion

Proposing a controlled trial protocol to verify the effects of COGNI-MACHINE computational thinking training on executive functions and other cognitive processes of children in the last years of primary school is relevant for the academic community since it will allow knowing the impact of study plans and programs aimed at teaching computational thinking, recognizing the type of activities that have more acceptability, adherence, and effectiveness in children of this age range as well as recognizing the differential impact that the teaching of computational thinking has on different executive cognitive processes.

One of the main strengths of this study will be the blinding of the evaluators to the allocation and the blinding of the investigators in charge of the intervention to evaluate the subjects. On the other hand, the novelty of the COGNI-MACHINE training, compared to other training, is that it seeks to take advantage of different types of activities to promote computational thinking, not only coding activities. This program includes, on the one hand, disconnected activities to introduce students to the development of more complex and abstract activities. On the other hand, it integrates different types of connected activities, starting with animation activities and game programming in the language of blocks, to later develop robotics projects applied to problem-solving.

One of the study's limitations is that, since the application context is school and integrated into the technology curricular program, individual randomization of the participants will not be possible. Therefore, the randomization will be conducted by groups. Additionally, given the nature of the study, participants will not be blinded to the intervention.

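### The satisfaction, acceptability, adherence and feasibility outcome falls under the 70% completion rule, so its main summary covers only children selected for attending

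*Protocol article*

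**What the plan says.** Under Secondary outcome measures, Table 5 has a row for "Satisfaction, acceptability, adherence and feasibility". Its instrument is a satisfaction and adherence scale built by the authors, rated as a "Likert scale with 4 response options". The Discussion says the trial should help in "recognizing the type of activities that have more acceptability, adherence, and effectiveness in children of this age range".

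Under Bias control, the attrition row of Table 3 states: "Data from participants who complete less than 70% of the training will be excluded from the study". Table 1, which sets out whose data enter the trial, has the same threshold as an inclusion criterion: "Children who have participated in 70% of the intervention". Neither table limits the rule to the cognitive tests, and the Table 5 row carries no exception.

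The same row of Table 3 goes on to announce data imputation and, in that connection, says "we will evaluate the difference of the results with the data of the excluded subjects and without them". Under Experimental group, the training is described thus: "The intervention comprises 24 sessions".

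**The concern.** An outcome that asks how well children accept and keep to a training needs the answers of those who did not keep to it. The stated rule takes those children out on the basis of their attendance, which is closely related to what the scale measures. Children who missed many sessions are plausibly less satisfied than the rest, so the average over those who remain is likely to be too favourable.

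This differs from the effect of the same rule on the between-group comparison of executive functions. A completer analysis of the cognitive tests might be argued for as a question about the effect in those who received the training. That argument does not carry over to a description of adherence, acceptability and feasibility.

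**Working it through.** **Inputs from the article.** 24 sessions (Experimental group); 70% completion threshold (Tables 1 and 3); four-option Likert scale (Table 5); usual dropout in this grade of about 15% (Recruitment). The article gives no figure for expected attendance, satisfaction, or the share of children below 70%, so there is no planned figure to reproduce on this point.

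**Step 1: what the threshold means in sessions.** 0.70 × 24 = 16.8. A child with 16 sessions has 16/24 = 66.7% and is excluded. A child with 17 has 17/24 = 70.8% and is kept. Any attendance figure computed on the retained children therefore has a lower limit of 17/24, whatever attendance was in the classes. This step needs no assumption.

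**Step 2: what it does to the scale score.** The Likert score is not truncated itself; it is averaged over children selected on a related variable. Assume satisfaction and attendance are jointly normal with correlation r, and that a fraction k with the highest attendance is kept. The mean satisfaction of the kept children then exceeds the mean of all children, in SD units, by

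bias = r × φ(c) / k, with c = Φ⁻¹(1 − k).

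| Fraction kept, k | c | φ(c) | φ(c)/k | r = 0.3 | r = 0.5 |
|---|---|---|---|---|---|
| 0.85 | −1.036 | 0.233 | 0.274 | 0.08 SD | 0.14 SD |
| 0.70 | −0.524 | 0.348 | 0.497 | 0.15 SD | 0.25 SD |

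The values of r and k are assumptions. The case k = 0.85 matches the 15% dropout under Recruitment only if the children lost to dropout are also those below 70%; the article does not equate the two. The case k = 0.70 shows a heavier loss.

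**Step 3: does another sentence undo the selection?** Table 3 first excludes the children and then announces a comparison of results with and without them. That comparison implies that their data are held. It is introduced as part of the imputation, and it does not name the Table 5 outcomes or make all allocated children the basis for them. The main summary remains the one on retained children.

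**The case against.** The strongest case against this point has four parts.

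1. **The listed outcome is a Likert score, not a session count.** A reader might infer that adherence, as an outcome, is at least 70% by construction. The article does not support that: the floor applies to sessions attended, and the scale score has none. This part stands, and it limits the point to selection on a related variable.

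2. **The bias is modest.** A reader might infer that the outcome could never show that the training is disliked or poorly attended. A shift of 0.08 to 0.25 SD does not do that. Children with 17 or more sessions can still rate the training low, and the number removed under the rule is itself evidence on attendance if it is reported. This part also stands. Sessions are built into curricular technology classes, and nothing in the article points to very low attendance.

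3. **The excluded children are compared.** It would be too strong to say that their data are deleted before the outcome is summarised, since Table 3 promises results with and without them. That is a partial mitigation, for the reasons in the third step of the working.

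4. **The choice of set for a descriptive summary belongs in the analysis plan, and correcting the 70% rule in general would settle it.** The first half does not stand, because the article does not leave the matter open: it fixes an exclusion in two tables without an exception. The second half is fair, but a revision that kept a completer analysis for the cognitive tests would leave this outcome affected unless it is named.

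It is also true that children who leave the school would not be recovered for the scale by any change in wording. If the 15% dropout were the whole loss, most of the bias in the scale score could remain.

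**Conclusion.** The point holds in a limited form. As written, the 70% rule covers the Table 5 row, so its main summary is taken over children selected on attendance and is likely biased upward. Under joint normality and an assumed correlation of 0.3 to 0.5, the size is about 0.08 to 0.14 SD with 85% kept and 0.15 to 0.25 SD with 70% kept. An attendance figure from the same set cannot be lower than 17 of 24. How far mean attendance would be overstated depends on an attendance distribution that the article does not give, so no figure is put on it.

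The outcome is secondary, and nothing here changes the sample size or the primary analysis. The correction is still worth making: it changes a stated rule, costs little, and supports the statements on acceptability and adherence that the Discussion anticipates.

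**What to change.** - State in Tables 3 and 5 that the 70% criterion does not apply to satisfaction, acceptability, adherence and feasibility, and word the Table 1 criterion to match.
- Summarise this outcome on all enrolled children in the classes assigned to COGNI-MACHINE.
- Offer the scale at post-test to all of these children still at the school, whatever their attendance, and report how many did not answer.
- Report the distribution of sessions attended out of 24 and the proportion of children reaching 17.

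**Cost.** The change is mainly one of wording. Attendance has to be recorded anyway to apply the 70% rule, and the scale is already in use. The reported figures may look less favourable. Children who leave the school will still be missing from the scale, so the number not answering should be shown beside the result.
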